## Abstract

**Objective:**

This study aims to increase self-awareness in patients with Parkinson’s disease (PD) using a newly developed mindfulness-based intervention, tailored for the specific needs of PD patients. Its impact on self-awareness and patients’ daily lives is currently being evaluated.

**Background:**

Recently, the phenomenon of impaired self-awareness for motor symptoms (ISAm) and some non-motor symptoms has been described in PD. ISAm can negatively influence patients’ daily lives, e.g., by affecting therapy adherence, and is therefore the main focus of this study. The main goal is the development of IPSUM (“Insight into Parkinson’s Disease Symptoms by using Mindfulness”), a PD-specific intervention for increasing patients’ mindfulness and thereby reducing ISAm.

**Methods:**

The effectiveness of IPSUM is evaluated by comparison of an intervention group with a waitlist-control group. A pre-post design with an additional 8-week follow-up measurement is applied, resulting in three measurement points: before, directly after and 8 weeks after completing the intervention protocol. In total, up to 180 non-depressed PD patients without severe cognitive impairment (non-demented) will be included. The primary outcome is a quantitative score for measuring ISAm. Secondary outcome measures are affective changes, neuropsychological performance and self-awareness of cognition. At pre- and post-measurement an fMRI scan is performed to connect behavioral and neurobiological findings. At post- and follow-up-measurement each patient will take part in a semi-structured interview to explore IPSUM’s impact on self-awareness and patients’ everyday lives.

**Results:**

The conception of the intervention protocol is finished, the resulting 8-week program is presented in detail. It has successfully been tested in the first group of patients, their feedback so far was quite promising. Recruitment is ongoing and a first interim analysis will be performed once 30 patients have completed IPSUM.

**Conclusion:**

For the first time, the intervention protocol of IPSUM has successfully been tested in a group of PD patients. As the study goes on, more quantitative data is collected for statistical analyses to evaluate its effectiveness. More qualitative data is collected to evaluate feasibility and effectiveness. We hope for this intervention to be capable of reducing the patients’ ISAm and improving their quality of life on many levels.

## Introduction

Parkinson’s disease (PD) is one of the most common neurodegenerative disorders. Neural degeneration and loss of dopaminergic cells in the substantia nigra cause a lack of dopamine which ultimately leads to impaired motor functioning (Lill and Klein, 2017). Cardinal motor symptoms of PD include bradykinesia, rigidity and resting tremor (Postuma et al., 2015). As drug treatment commonly consists of dopamine replacement therapy, levodopa-induced dyskinesia might evolve over time (Rizek et al., 2016). Though PD is mainly classified as a movement disorder, the frequent occurrence of a wide range of non-motor symptoms has been recognized in recent years. They include sleep disturbances, autonomic dysfunction (e.g., constipation), hyposmia and psychiatric symptoms like depression, anxiety, hallucinations or impulsivity (Postuma et al., 2015).

The phenomenon of anosognosia for hemiplegia following a right hemisphere stroke is well known. The term anosognosia refers to a complete lack of self-perceived neurological or neuropsychological deficits. A partial absence of this ability is defined as impaired self-awareness (ISA) (Prigatano, 2014). Though rarely considered in the past, more recent research describes the phenomenon of impaired self-awareness for motor impairment (ISAm) in non-depressed, non-demented patients with Parkinson’s Disease (for an overview see Maier and Prigatano, 2017). ISA is associated with lower therapy adherence, as well as higher patient mortality and caregiver burden and is therefore of high clinical relevance (Prigatano, 1999; Koltai et al., 2001; Appelros et al., 2007; Turró-Garriga et al., 2013).

ISAm in PD patients has mostly been studied for levodopa-induced dyskinesia (LID) ISAm for hyperkinetic movements has also been described for other diseases such as Huntington’s disease and schizophrenia (Vitale et al., 2001; Emsley et al., 2011; Sitek et al., 2014). Depending on the used measurement method, the prevalence of ISAm for LID in PD was found in up to 91% of patients with dyskinesias (Vitale et al., 2001; Maier et al., 2015). ISAm-LID in PD is associated with higher disease duration (Amanzio et al., 2010; Maier et al., 2016), higher levodopa equivalent daily dose (Amanzio et al., 2010; Maier et al., 2016) and predominantly left-sided symptoms (Pietracupa et al., 2013). Positron emission tomography using ^18^F-Flourodeoxyglucose (FDG-PET) has shown a positive correlation between ISAm-LID and higher glucose metabolism in brain areas which are considered important for the development of LID; mainly in the left putamen, the left supplementary motor area and the left pre-supplementary motor area (Maier et al., 2016).

On the other hand, ISAm for hypokinetic movements (resting tremor and bradykinesia) is prevalent in patients with and without dopaminergic medication (ON- and OFF-state). ISAm for hypokinetic movements (ISAm-Hypo) was found in 42–54% of patients in the ON-state, and in 24–55% of patients in the OFF-state (Maier et al., 2015, 2016). Maier et al. (2016) report a positive correlation of ISAm for hypokinesias in the ON- as well as the OFF-state, but no correlation between hypokinetic movement severity and the severity of ISAm-Hypo. Concerning dopaminergic states, ISA scores in the OFF state have been associated with left-sided disease onset and worse left-sided symptoms, while in the ON-state no findings could support this relationship.

There are two theories surrounding the underlying mechanisms of ISA. It is suggested that the underlying mechanism for ISAm-Hypo might differ from the mechanism for ISAm-LID (Maier and Prigatano, 2017). For once, similar to ISA in other diseases like traumatic brain injury and Alzheimer’s Disease, right hemispheric dysfunction may cause ISAm in PD (Prigatano, 2014; Shany-Ur et al., 2014). Examining glucose metabolism in the FDG-PET study Maier et al. (2016) have found a significant association between ISA scores in the OFF-State and hypometabolism in the right inferior frontal gyrus. They also report a tendency for significance in the right insular cortex. Both regions have not only been linked to anosognosia for hemiplegia in stroke patients (Kortte et al., 2015; Moro et al., 2016), but also to ISA of overall functional competency in dementia (Shany-Ur et al., 2014). The right inferior frontal gyrus and the right insula are part of a brain network which has been associated with motor response inhibition and action monitoring and might therefore be affected in PD patients with ISAm (Fotopoulou et al., 2010; Moro et al., 2016).

Contrary to the theory of right hemispheric dysfunction, it is hypothesized that ISAm-LID emerges as a consequence of dopaminergic overstimulation (Vitale et al., 2001; Amanzio et al., 2010, 2014). While dopamine replacement therapy compensates the lack of dopamine in mesocorticolimbic pathways, and therefore enhances executive functioning, medial-prefrontal ventral-striatal circuits might be overstimulated as they are less affected by dopamine depletion (Maier and Prigatano, 2017). This might result in impaired executive functioning like attentional set shifting, response inhibition and performance monitoring. Amanzio et al. (2011) suggested that a dysfunction of the cingulate cortex, which is typically involved in action and performance monitoring, contributes to the phenomenon of ISA. Although ISAm-LID has been associated with lower cognitive performance by some researchers, contradictory findings have not shown any correlation of ISAm-LID and cognitive or executive performance in neuropsychological tests (Maier et al., 2012, 2016; Pietracupa et al., 2013).

Despite the growing research interest in ISA for motor symptoms in PD, it is worth mentioning that ISA might also exist in regards of cognitive impairment (ISAc), mainly for memory and executive impairment (Kudlicka et al., 2013; Lehrner et al., 2015). Pillai et al. (2018) conclude that impaired self-appraisal for cognitive functioning is equally likely to occur in PD patients with mild cognitive impairment (MCI) and patients with amnestic MCI, which often progresses to Alzheimer’s Disease. Orfei et al. (2018) have highlighted the importance of the general level of cognitive functioning. They found higher anosognosia in PD patients with dementia and multi-domain MCI compared to PD patients with single-domain MCI or normal cognitive functioning. Interestingly, greater anosognosia might also be associated with depression and lower executive functioning. It has to be noted though, that other researchers have not found any evidence for ISAc in PD (Starkstein et al., 1996; Sitek et al., 2011, 2013; Koerts et al., 2012). In their review, Maier and Prigatano (2017) have suspected the use of different methods to assess ISAc, sample differences, as well as the potential importance of a present cognitive impairment to be reasons for these conflicting results. Future research should therefore comprise extensive neuropsychological test batteries and imaging data to get further insight into the phenomenon of ISAc. It is worth mentioning that newer research has already taken some of these aspects into consideration (Orfei et al., 2018; Pillai et al., 2018).

To study anosognosia for memory impairment in Alzheimer’s Disease Vannini et al. (2017) calculated an anosognosia index to quantify the discrepancy between subjective and objective memory scores. Using this method, they found decreased memory awareness in patients with amnestic mild cognitive impairment in comparison to a healthy control group. Among others, they also reported an association between lower memory awareness and reduced glucose metabolism in the posterior cingulate cortices and the hippocampus. Maier et al. (in preparation) applied a similar method to study differences of cognitive awareness between PD patients with and without MCI and healthy controls. For PD patients as a whole, they found an association between higher impairment of awareness and reduced metabolism in FDG-PET in the anterior and mid-Cingular cortices. Specifically, for PD patients with MCI they report the same association in the mid-Cingular cortex as well as the right superior temporal area and parts of the adjacent insular cortex. Taking neurobiological findings of ISAm and ISAc in consideration, the cingulate gyrus, as well as the (right) insula seem to play an important role regarding the general development of impaired self-awareness.

The concept of mindfulness originated in Buddhism, but has grown in popularity in western civilization and scientific research for several years (Kabat-Zinn, 2013; Fox et al., 2016). It has been formerly described as “paying attention in a particular way: on purpose, in the present moment, and non-judgementally” (Kabat-Zinn, 2004, p. 4). Mindfulness can be understood as a kind of personality trait, which can be improved by regular formal or informal mindfulness practice (Keng et al., 2011). While formal practice involves meditation or yoga practice, informal practice comprises all sort of daily activity which is performed while maintaining the described mindful attitude (Kabat-Zinn, 2013; Schug, 2016).

In general, mindfulness is strongly associated with variables of psychological health like quality of life, feelings of vitality and autonomy or optimism (Brown and Ryan, 2003; Rasmussen and Pidgeon, 2011). On the other hand, it is negatively associated with depression, social anxiety or other psychiatric symptoms (Brown and Ryan, 2003; Baer et al., 2006; Dekeyser et al., 2008; Cash and Whittingham, 2010; Rasmussen and Pidgeon, 2011). For more detailed information see Keng et al. (2011). Similar results have been reported for meditation practice alone, which is an essential part of most intervention concepts. While meditation practice seems to reduce negative emotions, like anxiety and stress, it might also enhance cognitive performance of attention and self-reflection (Sedlmeier et al., 2012). Further studies also hint at possible positive implications of mindfulness training on attention and possibly working memory and executive functioning (Chiesa et al., 2011).

Other studies also suggest positive implications in regards of body awareness. For example, early qualitative studies indicate a more positive self-representation and acceptance toward oneself as well as higher responsivity and intensity of body and emotional perception caused by regular yoga practice (Emavardhana and Tori, 1997; Daubenmier, 2005; Impett et al., 2006; Dittmann and Freedman, 2009). Additionally, long-term meditators showed an improved awareness and interpretation of body states (Tang et al., 2015), a higher coherence of emotional perception and physiological arousal, as well as more sensitivity for body sensations (Sze et al., 2010). In a study conducted by Fox et al. (2012), meditators reported more intense body sensations after completing a guided body scan meditation (in which the meditator focuses his/her attention systematically on different parts of the body) compared to a control group.

These behavioral findings regarding self-awareness and perception are also reflected on a neurobiological level. Early findings have suggested that meditators, compared to matched controls, display higher cortical thickness in the right prefrontal cortex and right insula. These areas have been associated with attention, introspection and processing of sensory stimuli (Lazar et al., 2005). In addition to higher cortical thickness, in a meta-analysis considering 21 studies, Fox et al. (2014) identified differences in volume and density of gray and white matter in various regions. Regions linked to self-awareness include the bilateral insula, somatomotoric cortices, the rostrolateral prefrontal cortex, and the anterior and mid-cingulate cortices. These regions have been mostly associated with abilities of introspection, metacognitive and body-oriented perception and self-regulation. According to the authors, especially changes in the area of the insula are central to general meditation practice, independently of the type of meditation practiced (Fox et al., 2014, p. 61). Although most studies have focused on cross-sectional comparisons between long-term meditators and novices, it is assumed that the effects regarding areas like the prefrontal cortex, the cingulate gyrus and the insula might be just as significant after only 8 weeks of mindfulness training (Gotink et al., 2016).

In a clinical context, many psychological mindfulness-based interventions exist. The most popular and most cited program is called Mindfulness-Based Stress Reduction (MBSR), which was developed by Jon Kabat-Zinn to improve stress and pain management in patients with chronic pain (Kabat-Zinn, 1982). In fact, the effects of MBSR and other mindfulness-based interventions have been studied in various physical chronic diseases, like Multiple Sclerosis, chronic pain or cancer. For those patient groups, positive effects have been found especially in regards of quality of life, stress and fatigue (Ott et al., 2006; Grossman et al., 2010; Rosenzweig et al., 2010). Larouche et al. (2015) have suggested that mindfulness-based interventions might slow down cognitive decline in patients with Alzheimer’s Disease.

In PD, some studies have already investigated the effects of mindfulness interventions in pre-post-designs. Participating in an intervention has led to an increase of mindfulness *per se*, an improvement of quality of life, as well as a reduction of negative emotions like depression, anxiety and stress (Pickut et al., 2015; Advocat et al., 2016; Cash et al., 2016; Dissanayaka et al., 2016). Cognitive functioning might also be positively influenced as improvements of attention, mental flexibility and self-reported ability of speaking have been reported (Cash et al., 2016). The only neurobiological study in a PD population investigating mindfulness was published by B. A. Pickut et al. (2013) who found an increase of gray matter density in the right and left hippocampus and part of the right amygdala. However, the authors postulate the need for more studies to clarify the neurobiological changes caused by mindfulness training in PD. Moreover, McLean et al. (2017) criticized methodological flaws for most behavioral studies, too. Hence, they have not been able to conduct a meta-analysis regarding the impact of mindfulness in PD patients and also emphasize the need for more studies of high quality. In addition, Rodgers et al. (2019) recently conducted a pilot trial to test the efficacy of a modified protocol of mindfulness-based cognitive therapy (MBCT) for reducing depression. For patients participating in a 6-week MBCT intervention, they report a significant reduction in depressive symptoms. Though no reduction of anxiety or improvement of quality of life was found, the results of this study suggest that mindfulness-based interventions can potentially be helpful to fight depression in PD patients.

To the best of our knowledge, so far, no study has investigated the effects of mindfulness on ISA in PD patients. The aim of this study is to get better insight into the effects of mindfulness training on impaired self-awareness in PD. Therefore, we present IPSUM, a protocol for a newly developed mindfulness-based intervention to increase self-awareness in PD. IPSUM, an acronym for “Insight into Parkinson’s Disease Symptoms by using Mindfulness,” is an 8-week intervention, whose development has been influenced by existing mindfulness-based programs as well as previously reported experiences with mindfulness interventions in groups of PD patients. IPSUM is innovative because (1) it is tailored for the specific needs of PD patients (2) educates about the use and practicability of mindfulness specifically in PD and (3) has a larger focus on the aspect of self-awareness and its implications for daily living compared to other mindfulness interventions. It takes into account the specific needs and impairments of PD patients, such as a reduced attention span, impaired executive functioning and lesser mobility.

We expect this new intervention to increase mainly impaired self-awareness for motor symptoms, but also to affect cognitive ISA. Based on the described general mindfulness literature, we assume several factors involved for mindfulness training to be an effective way to increase self-awareness in PD patients. For once, training the ability to describe one’s own perception (instead of judging it) might affect the patients’ view on their own body (Daubenmier, 2005). As they start being more focused on the present moment (e.g., during mindfulness meditation and yoga exercises), they also should be more aware of their body movements and posture as well as other internal sensations (including their thoughts and emotions). Achieving and maintaining this perceptional shift might be facilitated by increasing acceptance toward themselves and their disability, regular attention training in form of mindfulness meditation and improved emotion regulation of unpleasant emotions (Cayoun, 2005; Tang et al., 2015). As described earlier, neurobiological studies reported structural changes of brain regions associated with abilities of introspection, meta-cognitive and body-oriented perception and processing of sensory stimuli (Lazar et al., 2005; Fox et al., 2014). Therefore, we expect neurobiological changes caused by regular mindfulness training to strongly support the training of self-awareness. As the cingulate gyrus and the insula have shown to be central to ISAm and seem to be influenced by mindfulness practice, we are particularly interested in those areas.

In addition, as it seems typical for mindfulness interventions, we hope to find an increase of several aspects of emotional well-being (e.g., quality of life) while reducing negative emotions like depression, anxiety or stress and other PD-related non-motor symptoms (e.g., apathy or impulsivity). As mindfulness-related research has indicated, an increase of cognitive performance in dimensions that are impaired in PD, mainly attention and executive functioning, might also be possible. As neurobiological research for this specific field is practically non-existent, we also plan to perform resting-state fMRI and structural MRI scans to link behavioral and neurobiological data. To get more detailed information about changes relevant for the patients’ everyday life, a short semi-structured interview is planned.

## Methods

Patients with idiopathic PD (diagnosed according to the Movement Disorder Society PD criteria (Postuma et al., 2015) are recruited from the Department of Neurology, University Hospital Marburg, Germany. Up to 180 patients between 45 and 85 years of age will be included.

Exclusion criteria are depression [Beck Depression Inventory-2 – BDI-II score >19 (Beck et al., 1996; Hautzinger et al., 2006)], dementia [Parkinson Neuropsychometric Dementia Assessment – PANDA score <15 (Kalbe et al., 2008)] and a clinical diagnosis of additional severe neurological or psychiatric disorders. Patients with an advanced disease stage [i.e., Hoehn and Yahr scale, stage 5 (Hoehn and Yahr, 1967)] are excluded as they are not expected to be able to perform practical exercises during the intervention. Additionally, patients with prior regular experience in meditation or yoga are excluded as this study seeks to examine mindfulness novices. As this study seeks to improve an impaired self-awareness, patients must show signs of ISAm. This is checked by using a short screening tool. For all patients, antiparkinsonian medication is registered and has to be unchanged for at least 2 weeks prior to baseline measurement. Furthermore, patients’ eligibility to undergo an MRI scan is checked (though this is no exclusion criterion). The study has been approved by the local ethics committee of the University Hospital Marburg (Study number: 119/18) and registered at the German Clinical Trials Register (DRKS00015807). All patients have to give written informed consent prior to participation.

### Study Design

To evaluate the effectiveness of IPSUM on ISAm an adaptive pre-post-design is applied. First, eligible patients are randomized into an intervention group and a waitlist control group. After approximately eight to twelve patients have been successfully recruited, they are randomized by a computer program. Patients of the intervention group are measured at three points in time: before, directly after and 8 weeks after the intervention has ended. As stated before, the intervention takes place between the first two measurements and continues for 8 weeks. Patients of the control group are measured at the same time intervals, but do not take part in the intervention and are therefore treated as usual. For ethical reasons those patients can participate in the intervention after the study has ended. Figure 1 gives an overview of the course of the study.

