**FIGURE 1 F1:**
[figure not shown]
Course of the study for each patient.

At all three points in time ISAm is evaluated. Additionally, patients complete several questionnaires for emotional well-being. Cognitive functions are assessed using an elaborate neuropsychological test battery. Up to 30 patients will undergo a resting-state fMRI and structural MRI scan. Patients who have completed the intervention protocol can take part in an interview to report possible changes in their everyday life. For clarification, Figure 2 gives an overview of the tests performed at each measurement point. All patients, independent of their study group, complete all tests in the same order. For some neuropsychological tests parallel forms are available. For those tests, the applied version at each time point is randomly selected after a patient’s group assignment. It has to be noted, that all measurements are performed during the medication ON-state. Hereafter, primary and secondary outcomes, as well as all measurement procedures are further elaborated.

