### Outcome Measures

The main goal of this study is to increase self-awareness for motor symptoms. Therefore, the primary outcome for efficacy testing is a global ISAm-score. To be precise, mainly its change from baseline to post-intervention assessment is analyzed to evaluate the effectiveness of IPSUM. Changes of ISAm from baseline to follow-up are considered as a secondary outcome. However, we determined several other secondary outcomes like general neuropsychological test performance, the congruence between neuropsychological test performance and subjective daily life impairment (ISAc) and the congruence between objective neuropsychological test performance and subjective test performance (metacognition). Also, changes of several PD related symptoms (depression, apathy, impulsivity, sleeping problems) and affective states (stress, anxiety, quality of life, mindfulness) are analyzed. The aforementioned secondary outcomes comprise all changes from baseline to post measurement as well as changes from baseline to follow-up measurement. Additionally, structural neurobiological changes in the Insula and Cingulate Cortices, as well as any kind of reported subjective changes during the semi-structured interview are also considered when IPSUM’s effectiveness is evaluated.

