### Motor ISA-Assessment

A common method to evaluate self-awareness is by comparing self and outside assessments. In this study we use the recently developed and validated measurement method by Maier et al. (2015). The patient is shown several video clips where a healthy person demonstrates various movements. The task for the patient is to repeat the movement him/herself as seen in the video clip. The following 15 symptoms are examined:

1.Sitting on a chair: resting tremor (left and right hand), dyskinesia.2.Right hand pronation-supination: speed and amplitude of movement, dyskinesia.3.Left hand pronation-supination: speed and amplitude of movement, dyskinesia.4.Arising from a chair: resting tremor (left and right hand), dyskinesia.5.Walking down an aisle: resting tremor (left and right hand), dyskinesia.

The symptoms are distributed across the four subscales dyskinesia, resting tremor right hand, resting tremor left hand and bradykinesia. Following each task, the patient rates his/her performance on a dichotomous scale whether the movement was impaired or not. Regarding the perception of a symptom, in total each patient answers 15 questions with either yes or no. The whole procedure is recorded by video. Later, independent raters evaluate the movements as well. In case of any discrepancies – if the patient does not see any impairment, although the raters do – an impaired self-awareness is noted. For each symptom, irrespective of the patient’s awareness, they also rate its severity according to UPDRS-III (values range 0–4; 0 = normal/absent; 1 = mild; 2 = moderate; 3 = severe; 4 = unable to perform). This procedure allows the calculation of two independent scores: one score for overall motor impairment severity and a second score for ISAm severity. While the motor impairment score is calculated by summing up all motor severity ratings, the ISAm score is calculated by summing up all motor severity ratings of the potential 15 discrepancies. Hence, both scores can vary between 0–60. In the medication ON-state the ISAm global score can also be divided into subscores for impaired self-awareness for hypokinetic symptoms (ISAm-Hypo for tremor and bradykinesia) and hyperkinetic symptoms (ISAm-LID).

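### Randomisation is placed before the baseline assessment, so patients' self-rated baseline answers can be given with knowledge of their arm

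*Protocol article*

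**What the plan says.** Two places in the protocol article bear on the order of steps.

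- Study Design: "First, eligible patients are randomized into an intervention group and a waitlist control group". It continues: "After approximately eight to twelve patients have been successfully recruited, they are randomized by a computer program". The three measurements, beginning with the one before the intervention, are described only after this.
- The text under Figure 1, on tests with parallel forms: "the applied version at each time point is randomly selected after a patient’s group assignment".

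Three further statements determine why the order matters.

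- Study Design, on control patients: they "do not take part in the intervention and are therefore treated as usual".
- Outcome Measures, on the global ISAm score: "mainly its change from baseline to post-intervention assessment is analyzed to evaluate the effectiveness of IPSUM".
- Motor ISA-Assessment: "Following each task, the patient rates his/her performance on a dichotomous scale whether the movement was impaired or not". An item counts towards ISAm when the patient denies an impairment that the raters see, and it is weighted by the raters' severity score of 0 to 4.

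Planned Statistical Analyses also names the baseline measure and depression scores among the covariates. The Questionnaires section has every questionnaire completed at all three measurement points.

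**The concern.** In a waitlist trial, patients know their arm once they are told it. At post and follow-up nothing can be done about that. At baseline it can be avoided, but the stated order does not avoid it.

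The patient's contribution to the primary outcome is a series of subjective yes/no judgements about his or her own movements. A patient who knows that training in self-awareness is about to start may answer differently from one who knows that nothing will happen for 16 weeks (8 weeks to post plus 8 to follow-up). The same holds for the self-report questionnaires, which supply most of the affective secondary outcomes and a depression covariate.

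Baseline is meant to be the one measurement that allocation cannot have touched. If it is taken after patients know their arm, both uses of it lose that protection: as the starting point of the change score and as the adjustment covariate.

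**Working it through.** **1. Order of steps.** The article's sequence is: eligible, batch of about 8–12 recruited, randomised, measured. The rule for drawing test versions is consistent with this. If versions for each time point are drawn after assignment, the baseline version is too, so baseline testing follows assignment. That rule covers only the Regensburg verbal fluency test, the verbal learning and memory test and the MoCA. None of these enters ISAm, so the rule is evidence on the order and not a route of bias into the primary outcome. No sentence in the article puts baseline before randomisation. Figure 1 is not available to check.

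**2. Whether eligibility testing could already be the baseline.** Patients must be eligible before randomisation, so some screening comes first. For ISAm, the Methods section describes a short screening tool, not the 15-item video procedure. The BDI-II is both an exclusion criterion and a repeated questionnaire, and the article does not say whether the screening value is reused. The primary baseline is therefore not shown to be covered by screening.

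**3. Sensitivity of the score to one answer.** Inputs are from Motor ISA-Assessment: 5 tasks × 3 symptoms = 15 items, and 15 × 4 = 60, which reproduces the stated range of 0–60. For an item that raters score s (1 to 4), the contribution to ISAm is s if the patient says no and 0 if the patient says yes. One changed answer therefore moves the score by s, that is, by 1 to 4 points.

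**4. How a baseline shift carries through.** Let knowledge of allocation shift mean baseline ISAm by δ in the intervention arm relative to control, at baseline only.

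- Change score: (post_I − base_I − δ) − (post_C − base_C) = true contrast − δ.
- Baseline as covariate with within-arm slope β: (post_I − post_C) − β(base_I + δ − base_C) = adjusted contrast without the shift − βδ.

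Neither analysis removes δ (unless β = 0). The sign is open. If patients about to train look harder for symptoms, δ is negative and IPSUM appears less effective. If they are more inclined to deny symptoms, δ is positive and IPSUM appears more effective.

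**5. Illustration of scale (all bias values assumed).** Let b be a net bias in the between-arm contrast, in SD units of the analysed outcome. Take no true effect, 83 per group (Planned Statistical Analyses), a two-sided test at an assumed 5%, and a single analysis. Then SE = √(2/83) = 0.155, and the rejection rate is 1 − Φ(1.96 − b/SE) + Φ(−1.96 − b/SE).

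| Assumed b (SD) | Rejection rate |
|---|---|
| 0 | 5% |
| 0.1 | 9.9% |
| 0.2 | 25.2% |
| 0.3 | 48.9% |

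This shows only what a bias of a given size would do. The documents provide nothing from which b could be estimated.

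**The case against.** The strongest reply is that randomising is not the same as disclosing. A reader might infer that patients do know their arm at baseline. The article never says when they are told, and Figure 1 may show more. This stands as a limit: the text permits the problem but does not prove that it occurs. It does not remove the point, because the stated order creates the opportunity and no stated step closes it.

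A reader might also infer that the raters are unmasked and hear the patient's answers, from "The whole procedure is recorded by video. Later, independent raters evaluate the movements as well". The documents do not support that. They do not say whether the answers are oral or written, or whether raters see or hear them. Masking to arm and visit is simply not mentioned, and a condensed article commonly leaves such detail to the full protocol. The scoring method is also taken from a published, validated procedure that is not shown.

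A third inference would be that patients lost between allocation and baseline drop out of the intention-to-treat analysis. No such losses are described, and the article states a preference for intention-to-treat with dropout time and reason documented.

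Finally, reordering leaves knowledge of the arm at post and follow-up untouched, and that may be the larger patient-side problem. This is true. The article already acknowledges the lack of an active control. Only the additional exposure at baseline is avoidable.

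**Conclusion.** The point holds in a limited form. The article places randomisation before baseline, and nothing in it says that allocation is withheld until baseline is complete. The self-rated half of the primary outcome, and all questionnaires, can therefore be answered at baseline with knowledge of the arm. Any resulting shift passes into the change score in full and into a baseline-adjusted estimate in proportion to the slope.

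The size and direction of such a shift are unknown. It might be tempting to express it as a share of the effect the trial can detect, but the article gives no alpha, power, effect size or SD, so any such share would rest wholly on assumptions. The conclusion rests on the stated sequence and the absence of a stated delay in disclosure. It would fall if the full protocol or Figure 1 shows that baseline is finished before patients learn their arm.

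This is a cheap improvement to the design, not a demonstrated bias. Rater masking is a secondary matter for clarification and not an error shown by the article.

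**What to change.** Within each batch of about 8–12, complete the full baseline battery (video ISAm assessment, questionnaires, neuropsychology and, where applicable, MRI) for all patients. Only then run the randomisation and disclose the arm. Draw the test versions for all time points by patient ID beforehand, so that they do not depend on assignment. If disclosure is already held back until baseline is done, one sentence saying so is enough.

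The cost is scheduling: every baseline in a batch must be finished before its group can start, so the first patients assessed wait somewhat longer. No extra visits, staff or patients are needed, and the sample size does not change. Recruitment is described as ongoing, so the change can apply to batches not yet randomised. For batches already randomised, record whether baseline came before or after disclosure.

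Secondary: if the full protocol does not already do this, have the existing raters score coded clips without the patient's answers and without knowledge of arm or visit. The editing is not trivial at full size, at most 5 tasks × 3 visits × 180 patients = 2,700 segments, but it needs no additional raters.
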